## Abstract

*Introduction*. Atopic dermatitis (AD) and diarrhea-predominant irritable bowel syndrome (IBS-D) are two recurrent diseases with limited effective treatments. In Chinese Medicine (CM) theory, they may share dampness pattern as the same dominant pathogenesis at a certain stage and, thus, can be treated with the same method. While Chinese herbal formula Huoxiang Zhengqi (HXZQ) has been reported as an effective dampness-resolving therapy for both AD and IBS-D, further high-quality clinical studies are still needed. In addition, HXZQ lacks accurate clinical positioning based on CM patterns. Therefore, we utilize a master protocol design to evaluate HXZQ for dampness pattern simultaneously in AD and IBS-D, with the aim of identifying the pattern-defined population of HXZQ. *Methods and Analysis*. This master protocol design includes two randomized controlled trials (RCTs) and a real-world observational study. Based on two registry cohorts of AD and IBS-D, patients with dampness pattern will be enrolled in the RCTs to receive either HXZQ oral liquid or a placebo for 4 weeks and then will be followed up for another 4 weeks, while patients with nondampness pattern will constitute the observational study and experience a 12-week follow-up. A total of 678 AD patients and 322 IBS-D patients will be recruited from 14 hospitals in China over a 3-year period. The eczema area and severity index (EASI) and the proportion of responders for adequate relief (AR) are the primary outcomes in AD and IBS-D, respectively. Analysis will be undertaken separately in each substudy, and then an overall analysis combining multiple subgroups will be performed to comprehensively investigate the effect of HXZQ. *Discussion*. This study will provide high-quality efficacy evidence of HXZQ for AD and IBS-D patients and give an example of postmarketing evaluation for CM products under the pattern dominating different disease research model. The study is registered with ChiCTR1900026700 and ChiCTR1900026837.

## 1. Introduction

Atopic dermatitis (AD) is an inflammatory skin disorder characterized by intense itching and recurrent eczematous lesions. The prevalence of AD has been increased worldwide for decades [1], and it was estimated to be 4.6% among adults in China [2]. Conventional medications for AD including topical corticosteroids and calcineurin inhibitors are often associated with unwanted side effects [3], while Chinese medicine (CM) has been reported to be well tolerated and has advantages in improving health-related quality of life in AD patients [4, 5]. Therefore, CM has been a common therapeutic option for AD in China.

Irritable bowel syndrome (IBS) is a group of functional gastrointestinal disorders characterized by abdominal pain that may be associated with changes in bowel habits [6]. It heavily diminishes patients' quality of life and increases healthcare costs. The pathophysiological mechanism of IBS remains unknown, so current available treatments are limited [7]. In China, diarrhea-predominant IBS (IBS-D) is the most common subtype of IBS, and the initial therapies for IBS-D involving antidiarrheal, dietary, and lifestyle adjustments are often ineffective [8]. Fortunately, CM with a long history of treating functional bowel disorders provides a promising therapy choice [9, 10].

In CM theory, AD and IBS-D are two different diseases but can share dampness pattern (Shi Zheng) as the same dominant pathogenesis at a certain stage [11, 12]. Dampness pattern is one of the most common CM pathological mechanisms and occurs in many diseases. The clinical manifestations of dampness pattern include mental fatigue, heavy sensation in the limbs and body, and sticky or greasy tongue coating. Moreover, following the CM therapeutic principle of “treating different diseases with the same therapy,” AD and IBS-D can be treated with the same dampness-resolving method if they are both manifested as dampness pattern. Chinese herbal formula Huoxiang Zhengqi (HXZQ) is a classic dampness-resolving prescription that has been widely used since the early twelfth century. Clinical studies have suggested that it may be a safe and effective treatment for both AD [13, 14] and IBS-D [15, 16]. However, given the inadequate design of these studies, the benefits of HXZQ remain unclear in these two diseases.

HXZQ is composed of Herba Pogostemonis (Huoxiang), Pericarpium Arecae (Dafupi), Perillae (Zisu), Rhizoma Pinelliae (Banxia), Pericarpium Citri Reticulatae (Chenpi), Cortex Magnoliae Officinalis (Houpo), Radix Angelicae Dahuricae (Baizhi), Poria (Fuling), Rhizoma Atractylodis Macrocephalae (Baizhu), Radix Platycodonis (Jiegeng), and Radix Glycyrrhizae (Gancao). Experiments have revealed that it could resolve dampness pattern in rat models through multiple approaches: normalizing gastrointestinal dysfunction [17], improving immune and metabolic functions [18], and regulating gut microbiota disturbance [19]. Currently, HXZQ is an over-the-counter (OTC) medication and has various dosage forms such as oral liquids, capsules, and pills [20]. Despite its rich history of human use, HXZQ still requires high-quality evidence of postmarketing evaluation when used as a Chinese patent medicine. In addition, it also lacks accurate clinical positioning based on CM patterns.

Hence, we utilize a master protocol comprising two randomized controlled trials (RCTs) and a real-world observational study to evaluate HXZQ oral liquid for dampness pattern in AD and IBS-D, respectively, with the aim of identifying the accurate pattern-defined population of HXZQ. Master protocol is defined as a single overarching protocol designed with multiple substudies [21]. It allows the research questions to be addressed in an efficient way by minimizing time and infrastructure costs as compared with conducting separate studies [22]. Meanwhile, this study is actually developed under the pattern dominating different diseases research model (Yi Zheng Tong Bing model), which takes CM pattern as the target of intervention and focusses on the correlation between CM patterns and disease outcomes [23, 24]. Thus, the resulting procedures of our research will also provide a reference for future studies.

## 2. Methods

### 2.1. Objectives

The primary objective of this study is to evaluate the efficacy and safety of HXZQ oral liquid for dampness pattern in AD and IBS-D, respectively. Secondary objectives include (1) establishing two cohorts of AD and IBS-D to provide a study population basis and facilitate a long-term follow-up; (2) exploring the correlations of disease outcomes and dampness pattern, as well as other CM patterns; (3) developing a feasible study procedure of postmarketing evaluation for CM products under the pattern dominating different diseases research model.

### 2.2. Study Design and Setting

This master protocol consists of two multicenter, double-blinded, randomized placebo-controlled trials and a real-world observational study (Table 1): the CHARM trial (the Chinese herbal formula Huoxiang Zhengqi for atopic dermatitis with dampness pattern) [25] and the CHAIRS trial (the Chinese herbal formula Huoxiang Zhengqi for diarrhea-predominant irritable bowel syndrome) [26]. At the beginning of this trial, two registry-based cohorts of AD and IBS-D will be established, where patients with dampness pattern will be enrolled in the RCTs, and patients with nondampness pattern will be retained in the cohort constituting a real-world observational study. Thus, dampness pattern will be contrasted with nondampness pattern.

A total of 678 AD patients and 322 IBS-D patients will be enrolled from 14 hospitals in China over a 3-year period. Patients in the RCTs will be randomized at a ratio of 1 : 1 to receive either HXZQ oral liquid or a placebo for 4 weeks and then be followed up for another 4 weeks, while patients in the observational study will experience a 12-week follow-up.  Figure 1 displays the study flowchart. This study has been approved by the Ethics Committees of each participating site. Substudies have been registered in the Chinese Clinical Trial Registry (ChiCTR1900026700 and ChiCTR1900026837). An independent data safety monitoring board (DSMB) will monitor the overall conduct of the trial and assess the safety and efficacy of study procedures.

CHARM, Chinese herbal formula Huoxiang Zhengqi for atopic dermatitis with dampness pattern; CHAIRS, Chinese herbal formula Huoxiang Zhengqi for diarrhea-predominant irritable bowel syndrome; AD, atopic dermatitis; IBS-D, diarrhea-predominant irritable bowel syndrome; HXZQ, Huoxiang Zhengqi oral liquid.

### 2.3. Participants

#### 2.3.1. Recruitment

Participants will be recruited via posters in hospitals and advertisements in social media. To ensure a feasible and efficient recruitment, two registry-based cohorts will be established at the beginning of this trial. Based on predefined diagnostic criteria [6, 27], patients who present to a participating clinical site for treatment of AD will be screened for the AD cohort, and patients with IBS-D will be screened for the IBS-D cohort. In this registry period, broad eligibility criteria will be used to expedite the screening process. Then, eligible patients in the cohorts will further be classified as either “the dampness pattern” or “the nondampness pattern” following CM pattern differentiation. Subsequently, patients with dampness pattern will enter one of the RCTs, while patients with nondampness pattern will participate in the observational study. To be eligible for the RCTs, patients must again be screened against the specific inclusion and exclusion criteria (Table 2). Screening and enrollment logs will record enrolled patients, the reasons for exclusion, and the reasons eligible patients who are not enrolled.

#### 2.3.2. Inclusion Criteria of the Disease Cohorts

Patients between 18 and 70 years of age;Informed consent obtained.

#### 2.3.3. Exclusion Criteria of the Disease Cohorts

Women who are pregnant, or lactating, or planning pregnancy;Those who are currently enrolled in a study or had participated in a clinical trial within the past three months (one month for AD patients);Anyone allergic to any medicine or ingredients used in the study;Those who are considered unsuitable for the study by investigators.

#### 2.3.4. CM Pattern Differentiation

Patients in the disease cohorts will be classified as either dampness pattern or nondampness pattern depending on their clinical manifestations. Qualified CM clinicians will perform the pattern differentiation following relevant criteria [28]. Patients will be diagnosed as dampness pattern when meeting two main symptoms and one minor symptom of the general manifestations, or with one main symptom and two disease-specific manifestations. Otherwise, the nondampness pattern diagnosis will be made.(1)General manifestations of dampness patternMain symptoms: mental fatigue; anorexia; loose stool or watery diarrhea; white sticky or greasy tongue coating.Minor symptoms: heavy sensation in limbs; abdominal distension; pale tongue or pale teeth-marked tongue; soggy pulse or moderate pulse.(2)Disease-specific manifestations of dampness patternAD: papules, papulovesicle, or blisters scattered over the limbs or other body parts; skin itching; white tongue coating.IBS-D: loose stool or watery diarrhea; abdominal pain; white sticky greasy tongue coating; weak pulse.

### 2.4. Interventions

#### 2.4.1. Study Drug

In the two RCTs for AD and IBS-D, the experimental group will receive HXZQ oral liquid (20 ml, twice a day, for 4 weeks), and the control group will take the matched placebo (20 ml, twice a day, for 4 weeks). The HXZQ oral liquid and placebo will be manufactured by Taiji Group Chongqing Fuling Pharmaceutical Co. Ltd. (Chongqing, China) in accordance with the requirements of China good manufacturing practice (GMP) guidance. The placebo will be similar to HXZQ regarding appearance, weight, taste, and packaging. Compliance will be assessed upon a review of the bottles returned by patients.

#### 2.4.2. Concomitant Medications

For AD patients in the RCT, topical daily use of moisturizers such as urea ointment is recommended and permitted. Cetirizine hydrochloride tablets will be used in case of intolerable itching, and the dosage and frequency should be recorded. Other effective medications (orally or externally) and phototherapy for AD are not allowed. For IBS-D patients enrolled in the RCT, intolerable abdominal pain or diarrhea can be treated with emergency medications prescribed by the clinician. The name and dosage of the medication should be recorded in the patient's diary. Besides, any other medications and CM physiotherapy (such as acupuncture, moxibustion, or cupping) that may be effective for IBS-D, or can relieve abdominal pain and diarrhea, are prohibited. Treatments in the observational study will be provided by clinicians according to patients' specific conditions, and medical records of each patient should be exactly documented.

#### 2.4.3. Randomization and Blinding

Eligible patients in each RCT will be equally randomized to receive either HXZQ oral liquid or placebo through an interactive web response system. A center-stratified random sequence will be created with SAS 9.2 (SAS Institute Inc., Cary, USA). The randomization will be independently performed and managed by the Institute of Basic Research in Clinical Medicine (IBRCM), China Academy of Chinese Medical Sciences (Beijing, China). Patients and researchers involved in the trial including clinicians, research assistants, outcome assessors, and statisticians will be blinded to treatment allocation. In the observational study part, patients will receive no experimental interventions of this study. Investigators will just document the medical records, and blinding is not required.

### 2.5. Outcome Measurements

#### 2.5.1. Primary Outcome

For all AD patients, the primary outcome is the change in the Eczema Area and Severity Index (EASI) scores from baseline to the end of treatment (4^th^ week). EASI is the core outcome measurement instrument for AD, and the higher the score is, the more severe the AD is [29]. For IBS-D patients, the proportion of responders for adequate relief (AR) is the primary outcome evaluating the degree of symptom alleviation [30]. Throughout the study, IBS-D patients will be weekly asked the question: “Has your irritable bowel syndrome pain and discomfort adequately relieved in the past week?” (yes/no). Responders are defined as those who answer “yes” for at least 50% of the time, for example, in the RCT, that is, 2 out of 4 weeks in the treatment period. The proportion will be separately analyzed in the treatment period and the follow-up period.

#### 2.5.2. Secondary Outcomes

The secondary outcomes for AD include numerical rating scale (NRS) in the pruritus, investigator's global assessment (IGA) scale, body surface area (BSA), Skindex-29 (a dermatology-specific quality of life instrument), EuroQol-5-Dimensions-5-Level (EQ-5D-5L), antihistamine use, and CM pattern. Besides, EASI-50 and EASI-75 will be assessed, which refer to an EASI score showing improvement exceeding 50% or 75% during the treatment period, respectively [25]. For IBS-D patients, secondary outcomes are the Irritable Bowel Syndromes Symptom Severity Score (IBS-SSS), the Irritable Bowel Syndrome-Quality of Life Questionnaire (IBS-QOL), EQ-5D-5L, CM pattern manifestations [26].

### 2.6. Safety Assessment

Adverse events (AEs) will be reported to the investigators following the ICH-E2A guideline [31], and the causality between AEs and interventions will be assessed according to the WHO-UMC System for Standardized Case Causality Assessment [32]. Any event classified as “severe” or “life-threatening” in severity is considered a serious AE (SAE) and must be reported to the research ethics committee within 24 hours. Safety laboratory tests (routine blood, routine urinalysis, biochemical indexes of liver, and renal function) and electrocardiogram examination will be regularly conducted at baseline and 4^th^ week in the RCTs. Abnormal changes in laboratory examination will be judged by clinicians whether they have clinical importance and can be considered an AE. Safety assessment in the observational study will follow the guidance of clinicians.

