#### 2.8.2. Statistical Methods

A statistical analysis plan (SAP) will be developed prior to the completion of the trial. All data will be analyzed by statisticians using SPSS 18.0 (IBM SPSS Inc., Armonk, New York, USA) and SAS 9.2 (SAS Institute Inc., Cary, USA), and two-sided *P* values <0.05 are considered statistically significant.

First, the analysis will be undertaken independently for each RCT [25, 26]. Baseline characteristics will be summarized using descriptive statistics and will be listed by groups. Efficacy analysis will be performed in both intention-to-treat (ITT) and per-protocol (PP) populations. Missing data will be processed with the multiple imputation method, and if necessary, sensitivity analysis will be used to explore the robustness of the results. For all outcomes, *t*-test or Mann–Whitney *U* test will be employed for continuous variables; Chi-squared test or Fisher's exact test will be used for categorical variables. The changes across time among outcomes will be analyzed by repeated measure analysis of variance. Center effect and other factors based on professional judgement like gender, age, and disease course will be adjusted by logistic regression model or Cox regression model. For safety assessments, comparisons of the incidence and severity of AEs or adverse drug reactions (ADRs) between the groups will be performed by Chi-square test, Fisher's exact test, or Wilcoxon rank-sum tests based on the data characteristics. Occurrences of AEs will be listed in a summary table containing the time of occurrence, severity, duration, adopted measures, causality assessment, and prognosis.

Second, the analysis of the observational study will be conducted for each of the two disease (AD and IBS-D) populations. To investigate the real-world based effectiveness in this part, some exploratory analysis methods will be adopted [35]. Briefly, baseline characteristics of these nondampness pattern patients will be described using univariate analysis to profile the general demographics, disease features, and medication uses for each disease group. Then, all outcomes will be analyzed and compared between different medication groups by propensity score matching (PSM). Safety assessments of observational part will follow the same procedures and methods as those in the RCTs.

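### Section 2.6 defines a serious adverse event by severity grade and gives no outcome criterion, so the 24-hour report follows intensity rather than consequence

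*Protocol article*

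**What the plan says.** Section 2.6 (Safety Assessment) opens with a guideline reference: "Adverse events (AEs) will be reported to the investigators following the ICH-E2A guideline [31". Causality is then assigned by the WHO-UMC system. The next sentence gives the rule for serious events. It begins "Any event classified as", names the two grades severe and life-threatening, and continues "in severity is considered a serious AE (SAE) and must be reported to the research ethics committee within 24 hours".

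Section 2.8.2 (Statistical Methods) treats severity as one descriptor of an adverse event among several. It plans "comparisons of the incidence and severity of AEs or adverse drug reactions (ADRs) between the groups" and adds a listing: "Occurrences of AEs will be listed in a summary table containing the time of occurrence, severity, duration, adopted measures, causality assessment, and prognosis".

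Section 2.4.2 (Concomitant Medications) foresees intense disease symptoms in both trials. For atopic dermatitis, "Cetirizine hydrochloride tablets will be used in case of intolerable itching". For IBS-D, "intolerable abdominal pain or diarrhea can be treated with emergency medications prescribed by the clinician".

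**The concern.** Severity describes how intense an event is. Seriousness describes what the event leads to or threatens. The two often go together, but neither implies the other: a moderate reaction can put a patient in hospital, and a severe headache can pass without consequence. Expedited reporting exists for the second property, and Section 2.6 triggers it on the first.

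Two things are at stake. The ethics committee may not receive, within 24 hours, an event with a grave consequence but a modest grade. In the other direction, the serious-event label goes to every intense event, so a reported number of serious events no longer has its usual meaning. Section 2.1 makes safety part of the primary objective, so the label should carry that meaning.

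**Working it through.** The document states no figure on this point, so there is none to reproduce. The check is a reading of every safety provision for a criterion of seriousness other than grade, followed by applying the printed rule to the possible cases.

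**Step 1: search for another criterion.**

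- Section 2.6: the only criterion is the grade, severe or life-threatening. The sentence on laboratory tests lets clinicians judge whether an abnormal change counts as an adverse event, but says nothing about seriousness.
- Section 2.7: covers data collection, monitoring by the DSMB, and auditing. It has no definition of a serious event.
- Section 2.8.2: lists time of occurrence, severity, duration, measures taken, causality and prognosis. Seriousness is not a separate item.
- Table 3: gives the visits at which adverse events are collected, with no classification.

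None of these names admission, prolonged stay, disability or any other outcome as a trigger.

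**Step 2: apply the rule as printed.**

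| Grade of the event | Leads to admission or lasting disability | No such outcome |
|---|---|---|
| Mild or moderate | Not covered by the rule; no 24-hour report | Not covered; no report |
| Severe | Serious; 24-hour report | Serious; 24-hour report |
| Life-threatening | Serious; 24-hour report | Serious; 24-hour report |

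The two outcome columns are identical in every row, so under the printed rule the outcome never affects the classification. The gap is the first cell of the mild or moderate row. The excess is the second cell of the severe row.

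**Step 3: ask what could fill the severe row.** Section 2.4.2 expects itching, abdominal pain or diarrhea bad enough to need medication. If such an episode is recorded as an adverse event and graded severe, it becomes a serious event by definition. The article does not say whether worsening of the underlying disease is recorded as an adverse event, so this consequence is conditional.

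**Step 4: scope.** The rule covers both randomized trials: 218 + 212 = 430 patients (Table 1). Its reach into the observational study (460 + 110 = 570 patients) is unclear. Section 2.6 leaves safety assessment there to the guidance of clinicians, whereas 2.8.2 says it follows the same procedures and methods as the trials.

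**The case against.** The best defence has three parts.

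*The sentence is a sufficient condition.* It says that events with these grades are serious, and it does not say that only these are. This is right as grammar, and a reader who infers that the protocol expressly excludes all other events goes beyond the text. But no second condition appears anywhere, so the grade is the only operative trigger. The defence also leaves the other fault untouched: even as a sufficient condition, the sentence makes every severe event serious.

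*ICH-E2A is cited in the same section, and fuller detail may sit in the subtrial protocols.* An article may properly leave a list of criteria to such documents. Here, however, the article prints a rule and attaches a mandatory deadline to it. The guideline is cited for how events are reported to the investigators, and the sentence on serious events does not refer back to it. Site staff reading 2.6 would apply the explicit rule.

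*The listing in 2.8.2 still captures measures taken and prognosis.* This stands. The outcome of an event is not lost from the data; what fails is its classification and its prompt report.

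Several stronger readings are tempting but unsupported:

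- That deaths would escape the report. A fatal event would probably be graded at least life-threatening. Admission or disability after a lower grade is the clearer gap.
- That severe itch or diarrhea always counts as a serious event. Section 2.4.2 uses intolerable symptoms as a reason for medication, not as an adverse-event grade, and the trials already capture these symptoms through outcome scales and medication records.
- That a planned comparison of serious events between arms is distorted. Section 2.8.2 plans comparisons of adverse events and adverse drug reactions, and names none for serious events.
- That the DSMB would be kept uninformed. The 24-hour rule concerns the ethics committee, and nothing limits the DSMB to events that meet it.

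**Conclusion.** The point holds as a rule that is wrong as written, rather than as detail missing from a condensed article. Section 2.6 equates severity with seriousness and ties expedited reporting to the grade. The misclassification can run both ways: events with serious consequences but a low grade are not reported within 24 hours, and severe events without such consequences are.

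The effect is confined to the classification and expedited reporting of serious events in the 430 trial patients. The number of events involved cannot be estimated, because the document gives no event rates and no grading scale. No efficacy analysis, sample size or power figure changes.

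The conclusion rests on two assumptions: that sites would follow the printed sentence, and that no document outside the article overrides it. If the subtrial protocols already hold an outcome-based definition, the article's sentence still conflicts with them and needs correcting.

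**What to change.** In Section 2.6, replace the sentence on serious events with a definition by outcome that applies whatever the severity grade, and reconcile it with the guideline already cited there. It should name the qualifying outcomes explicitly, including death, immediate threat to life, hospital admission or prolonged stay, and persistent disability. Tie the 24-hour report to the ethics committee to that definition.

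Keep severity as a separate attribute on the case report form and add a field for seriousness. In the safety tables of Section 2.8.2, tabulate serious events and severe events separately. State whether worsening of the underlying disease is recorded as an adverse event, and whether the definition also applies to the observational study, where 2.6 and 2.8.2 currently differ.

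The cost is a short amendment, one extra form field, and a few minutes within the site training that Section 2.7 already requires.
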